Hence, the limited number of studies investigating the effectiveness of treatments for young individuals with Complex PTSD underscores the need for further research [10]. In their position paper published in 2019, the ISTSS deemed treatment recommendations premature because of current knowledge gaps. This indicates a pressing requirement for research exploring the effects of trauma-focused treatment on adolescents with (symptoms of complex) PTSD resulting from (repeated) sexual abuse, maltreatment, and/or domestic violence. To address this research gap, the present study describes an RCT aimed at investigating the differences in treatment effects between two treatment approaches (i.e., phase-based versus immediate trauma-focused) in adolescents with (symptoms of complex) PTSD resulting from a history of repeated sexual and/or physical abuse during childhood.

The primary objective of this study is to compare the results of phase-based treatment with those of immediate trauma-focused (i.e., eye movement desensitization and reprocessing; EMDR) therapy using a two-arm randomized controlled trial design. The first aim is to determine whether immediate trauma-focused treatment is not worse than phase-based treatment in reducing PTSD symptoms. If trauma-focused treatment is found to be equally effective when applied, it could lead to significant reductions in treatment duration. Second, we aim to investigate whether the phase-based therapy approach yields superior outcomes compared to the direct trauma-focused condition in terms of Complex PTSD symptoms, including emotion regulation, interpersonal problems, and self-esteem. Additionally, we will examine comorbid symptoms and dropout rates as secondary outcome measures. The third objective of the current study is to identify potential moderators and predictors of dropout or treatment responses/non-responses under both treatment conditions. We hypothesize that the presence of affect dysregulation and interpersonal problems at the beginning of therapy will be associated with poorer outcomes in the direct trauma-focused condition. Finally, we will examine the relationship between the reduction of posttraumatic stress symptoms in adolescents and a decrease in self-reported parental/caretaker stress. This objective addresses the clinical assumption that managing parental stress should be prioritized before initiating PTSD treatment in adolescents.

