## Method

### Study design

This study entails a single-blind, randomized controlled trial with two arms: a phase-based treatment condition (TRAP followed by EMDR) and a trauma-focused treatment condition (EMDR only). In the TRAP-EMDR condition, participants receive 12 sessions of skills training (TRAP; the Dutch adolescents version of the STAIRS protocol), followed by 12 sessions of EMDR therapy. In the other condition, the participants receive 12 EMDR sessions. The two groups will be compared for several outcome variables before treatment, immediately after 12 sessions (post-treatment), and six months post-treatment (follow-up) (see Fig. 1). This study will be coordinated by the Karakter Academic Center for Child and Adolescent Psychiatry in the Netherlands. The study started in 2018, paused for seven months in 2020 due to COVID-19, and continued in September 2020. This study is ongoing and is expected to be completed by 2024.

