### Statistical analysis

Data will be analyzed using SPSS V.29.0 for Windows (SPSS Incorporated). Pretreatment group differences with respect to age, sex, ethnicity, and type of traumatic event will be assessed using independent-sample t-tests for continuous data and χ^2^ tests for categorical data. Before testing, we will check all the data according to the appropriate assumptions.

To answer the primary question, a repeated-measures ANCOVA will be conducted. Baseline scores will be included as covariates, time as a categorical variable, and treatment condition as a fixed effect. The intercept will be treated as a random effect. We will examine the residuals to assess the model assumptions and goodness-of-fit. *P-values* will be reported to four decimal places, with *P-values* less than 0.001 reported as *p* < 0.001. For all tests, we will use 2-sided *P-values* with alpha =  < 0.05 level of significance. As this is a non-inferiority trial, both intention-to-treat and per-protocol analyses will be performed.

To evaluate the secondary outcomes, a repeated-measures ANCOVA will be conducted for the total score on the ECR-RC, DERS, RSES, RCADS, CPTCI, CBCL, OBVL, and Y-OQ-30. Baseline scores will be included as covariates, time as a categorical variable, and treatment condition as a fixed effect. The intercept will be treated as a random effect. We examine the residual to assess the model assumptions and goodness-of-fit. Delta-scores for pre- to post-treatment (T1 and T3) will be calculated, and an independent sample t-test will be used to compare the TRAP + EMDR and EMDR-only conditions. For the calculation of effect sizes (Cohen’s *d*) for within-group effects, we will divide the difference in means between pre- and post-treatment by the standard deviation of the difference in means. *P-values* will be reported to four decimal places, with *P-values* less than 0.001 reported as p < 0.001. For all tests, we will use 2-sided *P-values* with alpha =  < 0.05 level of significance.

To determine PTSD symptom changes on the CRIES-13, we will analyze the data for all time points in a linear mixed model. Time, treatment condition, the interaction term time × treatment condition, and sex will be entered as fixed factors, and age as a covariate in the model. The impact of missing data on outcome measurements will be evaluated using different methods, such as Last Observation Carry Forward (LOCF) and Multiple Imputation (MI).

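### LOCF, named as a missing-data check, carries scores of different meaning in the two arms and can bias the CAPS-CA comparison in either direction

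*Protocol article*

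**What the plan says.** The missing-data statement closes the Statistical analysis section. It has the impact of missing data judged "using different methods, such as Last Observation Carry Forward (LOCF) and Multiple Imputation (MI". It follows the CRIES-13 model but speaks of outcome measurements in general, so I read it as covering CAPS-CA too.

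The primary analysis is stated separately: "To answer the primary question, a repeated-measures ANCOVA will be conducted". It has the baseline score as covariate, categorical time and treatment as a fixed effect, and "The intercept will be treated as a random effect". On analysis sets: "As this is a non-inferiority trial, both intention-to-treat and per-protocol analyses will be performed".

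The arms differ in length. Under Study design, in the phase-based arm "participants receive 12 sessions of skills training (TRAP; the Dutch adolescents version of the STAIRS protocol), followed by 12 sessions of EMDR therapy", which makes 24 sessions. "In the other condition, the participants receive 12 EMDR sessions".

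The Primary outcome section schedules CAPS-CA at T1, T3 and T4 in EMDR-only, and at T1, T2, T3 and T4 in the phase-based arm. Sample size and power sets the margin at 5 points and gives no dropout rate, overall or by arm. The objectives treat dropout as a result of interest: "Additionally, we will examine comorbid symptoms and dropout rates as secondary outcome measures".

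**The concern.** LOCF is sometimes kept as a supposedly conservative check. Here it has no known conservative direction, because the last score before T3 is a different quantity in each arm:

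- EMDR-only: always T1, before any treatment.
- Phase-based: T1, or T2 after TRAP and before any EMDR.

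Two forces then pull against each other. If more assessments are lost in the longer arm, more unimproved scores enter that arm, and EMDR-only looks relatively better. If T2 scores are already improved, phase-based dropouts are credited with a gain that EMDR-only dropouts cannot receive, and EMDR-only looks relatively worse.

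At stake is whether the sensitivity analysis can do its job. In a non-inferiority trial it should challenge the finding that EMDR-only is not worse. A check whose bias depends on unknown loss and T2 availability cannot do that. Agreement with the primary result would not be reassuring, and disagreement would be hard to interpret.

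**Working it through.** **Inputs from the protocol article.** Margin 5; SD 10.4; assumed true difference -1.82; equal allocation; 80% power; type 1 error 2.5%; design factor 0.75; 40% inflation to 38 per arm.

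**Reproducing the plan's figure.** 7.85 × 10.4² × 2 / (-1.82 - 5)² = 1698.1 / 46.51 = 36.5 per arm. Then 36.5 × 0.75 = 27.4, and 27.4 × 1.4 = 38.4, stated as 38. The figure reproduces and nothing below changes it. If the whole inflation were for dropout, it would cover 1 - 27.4/38 = 28% loss. The article also assigns it to clustering and unknown psychometric properties, so no dropout rate can be read from it.

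**My assumptions.** D = mean improvement in EMDR-only completers, taken as 15 (10 and 20 also tried). δ = true deficit of EMDR-only, so phase-based completers improve by D + δ. pA, pB = share without a T3 score in EMDR-only and phase-based. f = share of phase-based dropouts with a T2 score. m = share of the full improvement reached by T2, taken as 0.5.

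**Formula.** Under LOCF the mean change at T3 is -D(1 - pA) in EMDR-only and -(D + δ)[1 - pB(1 - f·m)] in the phase-based arm. For EMDR-only minus phase-based:

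bias = D·pA - (D + δ)·pB·(1 - f·m)

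Negative values favour non-inferiority. With δ = 0 that happens only if pB(1 - f·m) > pA.

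**No true difference (δ = 0), D = 15**

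| Loss, EMDR-only / phase-based | f = 0 | f = 0.5 | f = 1 |
|---|---|---|---|
| 15% / 30% | 2.25 - 4.50 = -2.25 | 2.25 - 3.375 = -1.12 | 2.25 - 2.25 = 0 |
| 20% / 20% | 3 - 3 = 0 | 3 - 2.25 = +0.75 | 3 - 1.5 = +1.5 |

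With D = 10 the first row runs from -1.5 to 0 and the second from 0 to +1.0. With D = 20 they run from -3.0 to 0 and from 0 to +2.0.

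**True deficit at the margin (δ = 5), D = 15**

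| Loss, EMDR-only / phase-based | f = 0 | f = 0.5 | f = 1 |
|---|---|---|---|
| 15% / 30% | 2.25 - 6.0 = -3.75 | 2.25 - 4.5 = -2.25 | 2.25 - 3.0 = -0.75 |
| 20% / 20% | 3 - 4 = -1.0 | 3 - 3 = 0 | 3 - 2 = +1.0 |

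With equal 20% loss and only T1 carried, a 5-point deficit is shown as 4. With 10% against 40% loss and f = 0.5, the bias is 1.5 - 6.0 = -4.5.

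**Chance that the LOCF analysis declares non-inferiority.** The adjusted SD is 10.4 × √0.75 = 9.01, and the standard error is 9.01 × √(2/38) = 2.07. The chance is Φ((5 - LOCF difference)/2.07 - 1.96). This is a normal approximation that ignores LOCF's effect on the variance.

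| True difference, loss | f = 0 | f = 0.5 | f = 1 | Without bias |
|---|---|---|---|---|
| 5 (at margin), 15% / 30% | 44% | 19% | 5.5% | 2.5% |
| 5 (at margin), 20% / 20% | 7.0% | 2.5% | 0.7% | 2.5% |
| 0, 15% / 30% | 94% | 84% | 68% | 68% |
| 0, 20% / 20% | 68% | 54% | 40% | 68% |

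These describe the LOCF analysis alone, not the primary analysis.

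**The case against.** The strongest counter-argument is that LOCF appears once, as an example beside multiple imputation, for gauging the impact of missing data. The primary question is answered by a random-intercept model in two analysis sets, and no conclusion is tied to LOCF. That stands, and it limits the point to the sensitivity analysis.

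A reader might infer more: that the 24-session arm must lose more participants, so LOCF always tilts the result towards non-inferiority and would confirm the primary finding whatever the truth. The document does not support this. It states no loss by arm. Stopping sessions is also not the same as missing an assessment, and an intention-to-treat analysis is planned. With similar loss and improved T2 scores carried, the bias runs against EMDR-only. The -2.25 figure is the extreme in which no phase-based dropout has T2.

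The argument is also specific to CAPS-CA at T3. For CRIES-13, collected each session, LOCF carries the latest session score. At T4, participants lost after T3 carry a post-treatment score in both arms. There LOCF assumes no change after T3, which sits poorly with the Discussion's interest in delayed effects, but it is not the same asymmetry.

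Finally, the details of imputation belong in an analysis plan that is not shown, so their absence is no fault. The point rests only on the method that is named.

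**Conclusion.** The point holds in a limited form. LOCF is neither neutral nor reliably conservative for CAPS-CA at T3, because the score carried forward has a different meaning in each arm. It favours non-inferiority if assessment loss is sufficiently higher in the longer arm, or if a true deficit is shrunk because T1 is carried. It works against non-inferiority if loss is similar and improved T2 scores are carried.

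Under the stated assumptions and no true difference, the shift runs from -2.25 points (45% of the margin) to +1.5 points (30% of it). It is larger at a true deficit of 5 with unequal loss. Loss by arm, improvement, T2 availability and the gain by T2 are all assumed; only the margin, SD, sample size and assessment schedule come from the article.

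The planned primary result is not shown to depend on LOCF. This is a modest correction to the sensitivity analysis, worth making because it is cheap.

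**What to change.** In Statistical analysis, delete LOCF from the missing-data sentence and keep the repeated-measures mixed model as the main analysis. In its place:

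1. Use multiple imputation separately by arm, with T2 CAPS-CA (phase-based arm) and session-level CRIES-13 (both arms) as auxiliary variables. With 38 per arm, enter CRIES-13 as a few summaries rather than every session.
2. Add a delta-adjusted tipping-point analysis that worsens imputed EMDR-only scores by 0 to 5 points and reports where non-inferiority is lost, or that it is not lost in that range. For scale, 5 points applied to 20% imputed scores moves the arm mean by 0.20 × 5 = 1.0 point.

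This tests the claim in the direction that matters whichever arm loses more participants. The cost is a few extra analysis runs and a change of wording. It needs no new data, visits or participants.

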### Adverse events

Adverse events (AE) are defined as any undesirable experience occurring to a subject during the study, whether considered related to undergoing dietary treatment. All adverse events observed by the researchers or reported by the participants will be recorded and processed according to legislation in The Netherlands. A serious adverse event (SAE) is an event that 1) results in death, 2) is life-threatening (at the time of the event), 3) requires hospitalization or prolongation of existing inpatient hospitalization, 4) results in persistent or significant disability or incapacity, 5) is a congenital anomaly or birth defect, and 6) may jeopardize the participant or may require an intervention to prevent one of the outcomes listed previously. All SAEs will be communicated to the coordinating investigator (first author), who will be responsible for reporting this information through the web portal ToetsingOnline to the accredited MREC that approved the protocol. Reporting of SAEs that are life-threatening or result in death will be reported no later than seven days after the first knowledge of SAEs in a preliminary report. The final report will be completed no later than eight days after the preliminary report. All AEs will be monitored until they diminish or reach a stable state. Follow-up may require 1) medical procedures, 2) additional tests, or 3) referral to a general physician or medical specialist. SAEs need to be reported until the end of the study in the Netherlands, as defined in the protocol.

## Discussion

The present paper describes the rationale, study design, and methods of the MARS-study: an RCT evaluating the effects of a phase-based treatment model compared to purely trauma-focused therapy in young individuals diagnosed with PTSD and on the possible symptoms of complex PTSD resulting from (repeated) sexual and/or physical abuse during childhood.

This study had several strengths. First, it sought to assess the effectiveness and efficacy of two widely utilized treatment models in a group of patients who are often overlooked in research owing to their complex symptomatology. To the best of our knowledge, an efficacy study of adolescents who have experienced (repeated) sexual and/or physical abuse during childhood is unprecedented. Second, although a phase-based trauma-focused model has recently been studied in adults (15–17), no similar study has been conducted in adolescents. Research on the effectiveness of trauma treatment in adolescents (symptoms of complex) PTSD is limited [20]. To our knowledge, this is the first randomized controlled trial to investigate and compare the effects of regulation skill training with those of a direct trauma-focused treatment approach in this population. Third, adding a follow-up period allows us to track the long-term effects of both treatments, which can provide valuable information about the sustainability of the treatment effects and whether there are any delayed or long-term benefits (sleeper effects) or side effects. Therefore, we can make more reliable and comprehensive conclusions regarding the effectiveness of and differences between interventions. Additionally, by adding a mid-treatment measurement, it is possible to investigate the effects of TRAP and better assess the added value of this phase-based treatment approach.

Although the proposed study has strengths, it is important to acknowledge several methodological issues that should be taken into consideration. First, the participants included in the study are those who have developed PTSD as a result of surviving (repeated) sexual and/or physical abuse during childhood. While our goal is to include individuals with Complex PTSD, the current study faces challenges due to the lack of reliable and validated instruments specifically designed to assess the complex manifestations of symptoms associated with complex trauma. Consequently, the study relies on trauma history as the primary criterion for inclusion rather than the comprehensive manifestation of complex trauma symptoms. However, as part of the secondary analyses, separate questionnaires are administered to assess domains related to Complex PTSD, including emotion regulation, interpersonal regulation, and negative self-image. Another important consideration pertains to the operationalization of the phase-based model. The concept of a 'phase-based model' can be interpreted differently, depending on various perspectives. In clinical settings, it encompasses more than one treatment protocol that focuses on skill development in regulation. For some clinicians, preparing patients for trauma-focused treatment requires a personalized approach that involves comprehensive psychoeducation, establishing a therapeutic alliance, and engaging with family members and trusted individuals. Training in regulation skills itself demands substantial time and effort from both the patient and therapist. However, it is crucial to note that the effectiveness of this approach has not been extensively studied, raising a limitation in our understanding of its impact and outcomes.

Finally, this study implemented a non-inferiority trial. A non-inferiority trial is a type of clinical research study that aims to demonstrate that a new treatment is not worse than an existing treatment by a prespecified margin. One benefit of this type of trial is that it allows for the evaluation of new treatments that may have advantages over existing treatments, such as fewer side effects or lower costs, even if they are not necessarily more effective. However, non-inferiority trials have limitations. One limitation is that they require a well-defined and clinically meaningful non-inferiority margin, which is challenging to determine. In addition, non-inferiority trials may be less likely to detect small but clinically meaningful differences between treatments, which could limit their ability to provide definitive conclusions regarding the relative effectiveness of different treatments.

## Conclusion

Treating adolescents with (symptoms of complex) PTSD stemming from (repeated) sexual and/or physical abuse during childhood is an immensely significant endeavor. However, there is a lack of consensus among trauma experts regarding the most effective approach. The current study is specifically designed to address this gap by evaluating the effectiveness of the proposed protocol. Through this research, we aim to generate additional and novel knowledge regarding trauma treatment. The findings of this study hold potential for important implications, offering valuable insights into the field of trauma treatment for severely traumatized adolescents.

## Data Availability

Data sharing is not applicable to this article, as no datasets were generated or analyzed during the current study. The final dataset will be available (anonymized) to other researchers at the end of the study. We will assess whether the aim of using the dataset is in conflict with our planned future publications. Otherwise, the dataset can be shared with other researchers.

## Abbreviations

A-DES: Adolescent Dissociative Experience Scale
AE: Adverse Event
CBCL: Child Behavior Checklist
CAPS-CA: Clinician-Administered PTSD Scale for Children and Adolescents
CCMO: Committee on Research involving Human Subjects
CRIES-13: Children’s Revised Impact of Event Scale
CPTCI: Child Post-Traumatic Cognitions Inventory
CTSQ: Child Trauma Screening Questionnaire
DERS: Difficulties in Emotion Regulation Scale
DSM-IV: Diagnostic and Statistical Manual of Mental Disorders (Fourth Edition)
DSM-5: Diagnostic and Statistical Manual of Mental Disorders, Fifth Edition
ECR-RC: Experiences in Close Relationships Scale-Revised Child version
EMDR: Eye Movement Desensitization and Reprocessing
ICD: International Classification of Diseases
ISTSS: International Society for Traumatic Stress Studies
MI: Multiple Imputations
NICE: National Institute for Health and Clinical Excellence
RCT: Randomized Controlled Trial
OBVL: Opvoedingbelastingvragenlijst
ORS: Outcome Rating Scale
PTSD: Post Traumatic Stress Disorder
RCADS: Revised Child Anxiety and Depression Scale
RSES: Rosenberg Self-Esteem Scale
SAE: Serious Adverse Event
SES: Socioeconomic Status
SRB: Safety Review Board
SRS: Session Rating Scale
TF-CBT: Trauma-Focused Cognitive Behavioral Therapy
TRAP: Training in affectieve en interpersoonlijke Regulatievaardigheden voor meervoudig getraumatiseerde Adolescenten Protocol
STAIR: Skill Training in Affective and Interpersonal Regulation, World Health Organization
WMO: Medical Research Involving Human Subjects Act
Y-OQ-30: Youth Outcome Questionnaire
